# **1. Background and purpose of the study**

Acute lumbar sprain (ALS) is a common musculoskeletal disorder, often caused by the abrupt overstretching of the muscles, fascia, and ligaments in the lower back due to external forces. It is characterized by severe pain and activity limitation in the lower back, which significantly impacts the patient's work and life. Therefore, quickly relieving symptoms in a short period of time is the main need of patients visiting the clinic.

According to the guidelines of the American College of Physicians, nonsteroidal anti-inflammatory drugs (NSAIDs) are recommended as the first-line pharmacological treatment for ALS, with diclofenac being the most commonly used NSAID. A study has shown that diclofenac began to have effects at approximately  $0.6 \pm 0.05$  hours after administration, with peak analgesia at  $2.7 \pm 0.24$  hours. Despite the convenience of oral administration, the delayed onset of action and moderate analgesic efficacy of NSAIDs limit their clinical application to some extent. Furthermore, there is guidance suggesting that non-pharmacological therapies can be used as a priority treatment, highlighting the importance of non-pharmacological intervention studies.

Auricular acupuncture (AA), as a form of traditional acupuncture therapy, offers potential advantages in pain management. Due to its simple treatment modality and rapid onset of action, it is particularly suitable for acute pain disorders in clinical practice. A previous study has shown significant pain relief with AA for lumbar pain, but limited efficacy for lumbar mobility disorders. Exercise therapy, commonly

utilized in the management of mobility disorders, has shown good efficacy for low back pain when combined with AA, significantly improving pain and function. However, there is a lack of rigorous randomized controlled trials to support the combination of AA with active exercise in the treatment of ALS, and further studies are required.

In this study, 128 patients with ALS will be recruited as study subjects, and sham auricular acupuncture (SAA) as control to observe the immediate efficacy of AA combined with active exercise for ALS.

## **2 Study design and principles**

### **2.1 Study design**

The study focuses on individuals with ALS, dividing them into the AA group and the SAA group. The aim is to study both intra-group (before and after treatment within each group) and inter-group comparisons (between the two groups).

### **2.2 Sample size**

This study is a superiority trial designed to assess whether AA combined with active exercise is more effective than SAA combined with active exercise for the treatment of ALS. A previous study showed that VAS scores decreased by  $4.6 \pm 1.0$  and  $2.7 \pm 1.0$  after 10 minutes of acupuncture combined with exercise and sham acupuncture combined with exercise for ALS, respectively. Based on the results of this study, we predict that the change in VAS scores post-treatment will be  $4.6 \pm 1.0$  in the AA group

and  $2.7 \pm 1.0$  in the SAA group, with  $\alpha=0.025$  (unilateral),  $\beta=0.1$ ,  $\Delta=1.3$ , and  $K=1$ .

The sample size calculation is based on the following formula:

$$n_c = \frac{(Z_{1-\alpha} + Z_{1-\beta})^2 \sigma^2 \left(1 + \frac{1}{K}\right)}{(\mu_T - \mu_C - \Delta)^2}$$

It was calculated that a minimum of 58 participants were needed in each group.

Taking into account the 8 percent dropout rate, we plan to recruit at least 128 participants for this study.

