## **2.3 Randomization method**

Participants will be randomly assigned to the AA group and the SAA group in a 1:1 ratio. To minimize selection bias, an independent statistician will use SPSS 28.0 (IBM, Chicago, IL, license code: f56b44b8d8e3562ad8a2) to generate random numbers. These numbers will be enclosed in opaque envelopes. Participants will choose one of these envelopes after agreeing to the principle of random allocation, which will determine their group assignment and the corresponding intervention method.

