### **11.1 Statistical analysis content and methods**

#### **11.1.1 Statistical analysis sets**

##### **11.1.1.1 Efficacy evaluation data set**

(1) Full Analysis Set (FAS): Includes all randomized participants. For cases not observed throughout the entire treatment process, the last observed outcome (last observation carry-forward: LOCF) is carried forward to the point of data missing. The number of participants evaluated for efficacy at the endpoint is consistent with the number at the start of the study. Comprehensive efficacy analysis is conducted using the Per Protocol Set (PPS) and the Full Analysis Set.

(2) Per Protocol Set (PPS): Includes participants who complied with the study treatment protocol, primarily those who can be measured for key indicators and have no major violations of the study protocol. Analyses of demographic and other baseline characteristics and other efficacy indicators are conducted using the PPS.

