#### **11.1.4 Efficacy evaluation**

All efficacy evaluation data will be summarized separately according to the FAS and PPS sets, with the FAS set as the primary analysis method.

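### The stated 90% power against the 1.3-point margin is not assured under the LOCF rule in the primary FAS, and section 11.1.5 contradicts that rule by naming multiple imputation

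*Protocol*

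**What the plan says.** All references are to the Protocol.

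- **Section 2.2** calls the trial a superiority trial. It forecasts VAS changes of 4.6 (SD 1.0) with auricular acupuncture (AA) and 2.7 (SD 1.0) with sham (SAA). One-sided alpha is 0.025, beta 0.1, the margin 1.3 and the allocation equal. It finds 58 per group and continues: "Taking into account the 8 percent dropout rate, we plan to recruit at least 128 participants for this study".
- **Section 11.1.1.1** puts all randomised participants in the FAS. Where observation is incomplete, "the last observed outcome (last observation carry-forward: LOCF) is carried forward to the point of data missing". It adds: "The number of participants evaluated for efficacy at the endpoint is consistent with the number at the start of the study".
- **Section 11.1.4** summarises efficacy on both the FAS and the per-protocol set, "with the FAS set as the primary analysis method".
- **Section 11.1.5** specifies the primary ANCOVA, with baseline pain as covariate and group as factor. It assigns the missing data of withdrawn participants to chained-equation multiple imputation, and describes the ITT population as those who receive treatment. It does not mention the 1.3 margin.
- **Section 4.5** places the VAS assessments at baseline and at 2, 5 and 10 minutes, so a carried-forward value can only be the baseline, 2-minute or 5-minute score.

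**The concern.** Dividing by one minus the dropout rate makes up for observations that are lost. It leaves the analysed mean difference and SD as forecast. LOCF does something else: a participant without a 10-minute score stays in the analysis with an earlier one. If that score holds only part of the eventual change, the between-group difference shrinks and the spread within each arm grows. Section 2.2 allows for neither.

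The plan has little room for this. The forecast difference is 4.6 - 2.7 = 1.9 and the margin is 1.3, so the power rests on a net effect of 0.6 points. Some of the withdrawal reasons in sections 3.1.5 and 3.1.6 (ineffective treatment, adverse reactions, increased pain) make a partial carried change plausible.

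At stake is what the 90% describes. If the LOCF-filled FAS is primary and is tested against 1.3, a result that misses the margin could be read as coming from a 90%-power trial when the power was lower. With two missing-data rules in the text, a reader cannot tell which analysis the 90% belongs to.

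**Working it through.** **1. The plan's own figures** (inputs from section 2.2)

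n per group = (z for 1 - alpha + z for 1 - beta)² × SD² × (1 + 1/K) / (difference - margin)²
= (1.960 + 1.282)² × 1 × 2 / 0.6² = 58.4 (58.37 with unrounded quantiles).

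The stated 58 gives power 89.8%; 59 gives 90.3%. For dropout, 58 / 0.92 = 63.04, so 64 per arm and 128 in total, as stated.

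**2. Power if missing observations are simply lost**

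128 × 0.92 = 117.8 observed, or 58.9 per arm: power 90.2%. This is also roughly what multiple imputation should give if data are missing at random.

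**3. Power under LOCF with all 64 per arm kept**

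Assumptions that the protocol does not supply:
- p = 0.08 of each arm lacks the 10-minute VAS. The 8% is the plan's dropout rate; equating it with missing 10-minute scores is an assumption.
- The carried value holds a share f of that person's 10-minute change, with the same f in both arms.
- Dropout is unrelated to the size of the change.

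For an arm with full mean change mu and SD 1.0:
- mean = mu × (1 - p + p f)
- variance = (1 - p) + p f² + p (1 - p) × [mu (1 - f)]²
- power = Phi[(difference - 1.3) / sqrt((var AA + var SAA) / 64) - 1.96]

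Worked case, f = 0.5:
- Means are 4.6 × 0.96 = 4.416 and 2.7 × 0.96 = 2.592, so the difference is 1.824.
- Var AA = 0.92 + 0.02 + 0.0736 × 2.3² = 1.329.
- Var SAA = 0.92 + 0.02 + 0.0736 × 1.35² = 1.074.
- SE = sqrt(2.403 / 64) = 0.194.
- Power = Phi(0.524 / 0.1938 - 1.96) = Phi(0.744) = 77%.

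| f | Difference | SE | Power against 1.3 |
|---|---|---|---|
| 1 | 1.900 | 0.177 | 92.4% |
| 0.9 | 1.885 | 0.176 | 91.3% |
| 0.75 | 1.862 | 0.179 | 87.9% |
| 0.5 | 1.824 | 0.194 | 77.2% |
| 0.25 | 1.786 | 0.218 | 60.8% |
| 0 | 1.748 | 0.248 | 43.9% |

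Power equals 90% at f of about 0.83.

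An ANCOVA simulation (4,000 runs per case, baseline uniform on 4 to 8 and unrelated to change) gave 91.5%, 87%, 76.1% and 44.6% for f = 1, 0.75, 0.5 and 0.

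**4. Sensitivity to the other two conditions**

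- *Fewer missing scores.* If only 4% lack the 10-minute VAS, power is 90.3% at f = 0.75, 85.6% at f = 0.5 and 67.6% at f = 0.
- *No margin.* Tested against zero, power exceeds 99.9% at every f, including f = 0.

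**The case against.** The strongest reply is that no loss of power has been shown. It has five parts.

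- **LOCF is not the settled rule.** Section 11.1.5, which specifies the primary ANCOVA, names multiple imputation, and under that rule the 8% allowance is about right if data are missing at random. This stands. It is why the conflict between 11.1.1.1 and 11.1.5 belongs to the point. It does not remove the point, because LOCF is written into the definition of the primary set and 11.1.5 does not withdraw it.
- **Keeping dropouts costs nothing in itself.** With the full change carried, power at 64 per arm is 92.4%. This stands: the loss comes only from partial carried values, and the documents give no f.
- **The low figures need an unlikely pattern.** The 44% requires all 8% in both arms to have no score after baseline, in one session with 10 minutes of needle retention. Section 3.1.5 asks for the last data and any assessment that can still be done, and section 3.1.4 counts wrongly enrolled cases, who may have complete scores. This stands, and makes 44% an extreme bound. It does not dispose of the middle of the range, and 8% is the plan's own rate.
- **The ANCOVA as written carries no margin.** This is true, and against zero the matter disappears. But section 2.2 attaches beta = 0.1 to the 1.3 margin, so the stated power has to be judged there.
- **The arithmetic is sound.** This stands in full. A reader might infer that 58 or 128 is miscalculated, but both reproduce.

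**Conclusion.** The point holds in conditional form. The 90% in section 2.2 is about right for observed 10-minute data, or for multiple imputation with data missing at random. It is not assured for the LOCF-filled FAS. With 8% missing at 10 minutes and a test against 1.3, power under LOCF is 88%, 77% or 44% for f of 0.75, 0.5 or 0, and it is below 90% once f is under about 0.83. These figures rest on an assumed f, on all 8% lacking the 10-minute score, and on the margin being used in the test.

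A reader might go further and infer that the trial is underpowered, or that its primary analysis fails to deliver 90%. The documents do not support that: they give no f, they name a second missing-data rule under which about 90% holds, and their stated ANCOVA sets no margin. What they do support is that the power statement, the FAS definition and the missing-data rule do not fit together and need to be reconciled.

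**What to change.** Keep 128.

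1. Reconcile sections 11.1.1.1 and 11.1.5: in the FAS definition, replace LOCF with the chained-equation multiple imputation of 11.1.5 for the primary analysis. Keep LOCF at most as a sensitivity analysis. In the same edit, settle whether the primary population is all randomised or all treated participants.
2. State in section 2.2 that the 90% refers to that analysis, tested against the 1.3 margin.
3. If LOCF stays primary, remove the unqualified 90% from section 2.2 and give power over a range of f, with f and the share lacking a 10-minute score labelled as assumptions.

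The cost is protocol wording and slightly more analysis work, with no extra participants. Under option 3 the price is a less favourable stated power. Restoring 90% under LOCF by recruitment instead would take 69, 92 or 206 per arm for f of 0.75, 0.5 or 0 under the same assumptions, which is a further reason to prefer the imputation already named.

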## **2.3 Randomization method**

Participants will be randomly assigned to the AA group and the SAA group in a 1:1 ratio. To minimize selection bias, an independent statistician will use SPSS 28.0 (IBM, Chicago, IL, license code: f56b44b8d8e3562ad8a2) to generate random numbers. These numbers will be enclosed in opaque envelopes. Participants will choose one of these envelopes after agreeing to the principle of random allocation, which will determine their group assignment and the corresponding intervention method.

## **2.4 Blinding**

Participants, outcome assessors, and statistical analysts will be blinded to group assignments. Although acupuncturists will be aware of the treatment allocations, they will not participate in the subsequent outcome assessment or data analysis.

## **2.5 Control group**

The study establishes a SAA group as the control group.

## **2.6 Flowchart of the study procedure**

[figure not shown]

## 3 Study population

### 3.1 Participants with ALS

#### 3.1.1 Diagnostic criteria

ALS diagnosis is based on the "Clinical Diagnosis and Treatment Guidelines: Orthopedics" published by the Chinese Medical Association, which includes:

1. Definite trauma history and low back pain immediately after the injury;
2. Spasm of the lumbar muscles and limitation of movement;
3. Localized tenderness at the injury site;
4. No obvious abnormalities on imaging.

#### 3.1.2 Inclusion criteria

1. Meet the diagnostic criteria for ALS;

2. Unilateral low back pain, age 18-60 years;
3. Duration of the disease  $\leq 3$  days;
4. Moderate to severe pain, with the visual analogue score (VAS) between 4 and 8;
5. Signed the informed consent form.

### **3.1.3 Excluded criteria**

- (1) Combination of lumbar spondylolisthesis, lumbar spine tumor, fracture and other diagnosed definite pathological changes of the lumbar spine;
- (2) Low back pain caused by internal medicine diseases;
- (3) Coexistence of cardiovascular, hepatic, renal, pulmonary, and hematopoietic systems and other serious primary diseases;
- (4) Severe mental illness or intellectual disability, unable to cooperate with the completion of the questionnaire;
- (5) Women in pregnancy or breastfeeding;
- (6) Fear of acupuncture, or contraindications to acupuncture such as skin infection at the acupoint site;
- (7) Use of other analgesics within the past 6 hours.

### **3.1.4 Exclusion and dropout criteria**

- (1) Cases that do not meet the inclusion criteria and are erroneously included should be excluded.
- (2) Subjects with poor compliance who withdraw themselves during the treatment.
- (3) Cases that develop severe adverse reactions or complications, making it inappropriate to continue the treatment and thus terminating the trial.

### **3.1.5 Handling of excluded and dropped cases**

(1) Upon a subject's dropout, the supervising physician should inquire about the patient's reasons, record the last data, and complete the assessments that can be completed.

(2) For cases withdrawing due to adverse reactions or ineffective treatment, the supervising physician should take appropriate measures based on the actual conditions of the subjects.

(3) Fill out the "Treatment Completion Summary" and "Clinical Trial Completion Status" in the Case Report Form (CRF).

(4) All excluded or dropped cases should be analyzed for intention-to-treat at the end of the trial.

(Note: Intention-to-treat analysis (ITT) refers to including subjects in the effectiveness analysis of the group they were assigned to, regardless of whether they received the group's intended treatment.)

### **3.1.6 Case termination criteria**

(1) Subjects who experience increased pain or other severe adverse reactions during the study, making it inappropriate to continue participation.

(2) Subjects who request to withdraw from the clinical study midway.

(3) Patients who are uncooperative and non-compliant with treatment, despite repeated explanations by the clinician.

(4) Researchers should record in detail the reasons and timing of withdrawal from the study; cases that have surpassed half of the treatment duration should be included in

the efficacy analysis.

## **4 Interventions**

### **4.1 Acupoint selection**

Auricular point selection is based on prior studies and traditional auriculotherapy, which involves selecting auricular regions that correspond to body anatomical parts. The Lumbosacral Vertebrae (AH9) (Located on the body of the antihelix posterior to the Abdomen) will be selected. The auricular point will be positioned according to the World Federation of Acupuncture Societies Standard Acupoint Positioning, as depicted in Fig 1.

[figure not shown]

**Fig 1 Location of acupoint**

### **4.2 Appliance selection**

(1) Auricular needles: Use Seirin Corporation's single-use sterile microneedles, registration number: National Food and Drug Supervision and Medical Equipment (Import) No. 2012-2272550. Specifications are  $0.2 \times 1.5$  mm, see Figure 2A.

(2) Sham auricular needles: Same Seirin Corporation single-use sterile microneedles, registration number as above. Placebo needles look identical to real needles but lack a needle body and do not penetrate the skin, see Figure 2B.

[figure not shown]

**Fig 2. Auricular needle and Sham auricular needle**

### **4.3 Procedures**

(1) Auricular acupuncture group: Participants will be in a seated position. The acupuncturist will sterilize the skin of the healthy side AH9 with a 70% alcohol swab. Subsequently, a disposable auricular needle will be pierced vertically into the healthy side AH9. After needle insertion, moderate pressure will be applied to elicit the "de qi" sensation. Upon achieving "de qi", participants will be asked to stand. The acupuncturist will stand behind the participant and support the participant's waist. Then, the participant will be guided through moderate exercises, including forward bending, backward stretching, lateral bending, and rotation, all performed within the limits of their pain tolerance. The range and speed of these movements will gradually increase as the pain decreases.

(2) Sham auricular acupuncture group: This group will receive treatment with a placebo needle of the same shape which lacks a needle body and does not penetrate the skin but is merely taped at the acupoint. The treatment operation is the same as the AA group.

Participants in both groups will receive a single treatment session, with a 10-minute auricular needle retention time.

#### **4.4 Remedial pain management**

If patients experience intolerable lower back pain that does not improve post-treatment, they will take the non-prescription NSAID pain reliever ibuprofen. The dosage, time of administration, and the duration until pain relief are recorded.

#### **4.5 Observation period**

Baseline assessments will be performed before enrollment, and pain intensity and ROM evaluations will be conducted 2, 5, and 10 minutes post-treatment.

### **5 Observation indicators**

#### **5.1 General items**

Patient's name, gender, age, diagnosis, and course of illness will be recorded in the patient CRF.

#### **5.2 Biological indicators**

(1) Demographic signs: Gender, age, height, weight, occupation, marital status, and educational background.

(2) Vital signs: Body temperature, heart rate, breathing.

(3) Basic medical history and routine physical examination.

These indicators will be recorded at the time of enrollment.

## **5.3 Diagnostic indicators**

Chief complaints and clinical manifestations, medical history, physical examination; auxiliary examinations such as lumbar spine X-rays, CT, MRI will be conducted for disease diagnosis by the primary physician.

## **5.4 Measurement indicators**

### **5.4.1 Primary outcome**

The primary outcome will be the change in pain intensity from baseline to 10 minutes after treatment as measured using VAS scores.

### **5.4.2 Secondary outcomes**

(1) Changes in pain intensity at 2 and 5 minutes after treatment will also be measured using VAS scores.

(2) Lumbar range of motion (ROM) will be assessed at baseline, 2, 5, and 10 minutes during treatment. Participants will be instructed to stand with their feet slightly apart, shoulder width apart, and their body relaxed. Measurements will be taken for forward flexion, backward extension, right lateral flexion, and left lateral flexion in order.

(3) Patient expectations of treatment outcomes will be assessed at baseline using the efficacy expectations scale.

(4) The success of the blinding will be assessed at the end of treatment using a blinded questionnaire.

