#### **11.1.5 Statistical analysis methods**

This study utilizes SPSS 28.0 for the analysis of clinical data. Continuous variables with normal distribution will be expressed as mean  $\pm$  SD and continuous variables with non-normal distribution will be reported as median and interquartile range (IQR).

For analyzing demographic data, continuous variables will be analyzed using the independent samples t-test or the Wilcoxon rank sum test depending on whether or not they conform to a normal distribution. Categorical variables will be analyzed using  $\chi^2$  test or Fisher's exact test. All significant demographic differences will be included as covariates in subsequent efficacy analyzes. The primary outcome indicator will be analyzed using analysis of covariance with baseline pain levels as a

covariate and group as a factor. The secondary outcomes, including changes in pain intensity at other time points (2, 5 minutes) and ROM at different time points, will be analyzed using repeated measures ANOVA or Mann-Whitney U test, depending on the data's distribution. Additionally, correlations between pain VAS scores and efficacy expectation scores will be explored using Spearman's or Pearson's correlation analysis. We will follow the intention-to-treat (ITT) principle and analyze all participants who receive treatment. Missing data of withdrawn participants will be processed using chained-equation multiple imputation.

(1) Case Distribution: Size of different data sets in each group, distribution of cases across centers, detailed list of dropouts, discontinuations, and reasons.

(2) Comparability Analysis: Compare demographic data and other baseline values to assess comparability between groups.

(3) Compliance Analysis: Compare whether patients in each group followed the design protocol. Compliance is evaluated based on the records in the participant's CRF form, calculating percentages for <80%, 80%–100%, and >100% compliance.

(4) Factors Affecting Efficacy Analysis: If there are significant differences between groups before the study or factors significantly affecting efficacy, these factors should be considered as covariates in the group comparisons, requiring covariance analysis or logistic regression, and a detailed list of concomitant medication use.

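### Treatment expectation, measured only at baseline, is listed as a secondary outcome, and its one named analysis is a simple correlation that adjusts for neither group nor baseline pain

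*Protocol*

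**What the plan says.** Protocol 5.4.2 (Secondary outcomes), item (3): "Patient expectations of treatment outcomes will be assessed at baseline using the efficacy expectations scale". The protocol describes no later expectation measurement, and 4.5 places the baseline assessments before enrolment.

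Protocol 11.1.5 gives the score one named analysis: "correlations between pain VAS scores and efficacy expectation scores will be explored using Spearman's or Pearson's correlation analysis". The wording does not say whether VAS enters as a level or a change, at which time point, or whether the two arms are pooled.

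The primary model in the same section does not name expectation: "The primary outcome indicator will be analyzed using analysis of covariance with baseline pain levels as a" covariate, with group as the factor. Two further rules in 11.1.5 can add covariates. One covers demographic variables only: "All significant demographic differences will be included as covariates in subsequent efficacy analyzes". The other, item (4), is broader. Besides factors that differ between groups before the study, it covers "factors significantly affecting efficacy, these factors should be considered as covariates in the group comparisons".

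**The concern.** The first problem is classification. A secondary outcome should be something that the intervention could alter. A score recorded once, before treatment, cannot be altered by it, and any difference between arms on it would reflect chance in the allocation.

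The second problem is the choice of analysis. The primary endpoint is self-reported pain in a sham-controlled trial, so it is sensible to ask whether patients who expect more benefit report more. A simple correlation is a poor tool for that question. It ignores group, which is planned to shift the VAS change by 1.9 points. It also ignores baseline pain, which the inclusion criteria (3.1.2) allow to range from 4 to 8. If post-treatment VAS levels were used, differences in starting pain would enter the coefficient. The primary ANCOVA already handles both variables, so the better method is in the same section.

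At stake are how informative an exploratory analysis will be and a modest amount of precision. The validity of the group comparison is not at stake.

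**Working it through.** **Inputs from the protocol (2.2).** Expected VAS change is 4.6 in the AA group and 2.7 in the SAA group, with SD 1.0 in each. One-sided alpha is 0.025, power 0.90, margin 1.3, allocation 1:1. The within-arm correlation r between expectation and VAS change is not given, so it is assumed here over 0.1 to 0.4.

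**Step 1: reproduce the planned size.** n per group = 2 × (1.960 + 1.282)² × 1.0² / (1.9 − 1.3)² = 58.37. The protocol states: "It was calculated that a minimum of 58 participants were needed in each group". This agrees, although 58.37 rounded up would be 59. With 8% dropout, 58 / 0.92 = 63.04, so 64 per group and 128 in total, as planned. Power at 58 per group by the same normal approximation is 0.898.

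**Step 2: what pooling the arms would do to the correlation.** With equal arms and a difference of 1.9, the SD of VAS change across both arms is √(1.0² + (1.9/2)²) = √1.9025 = 1.379. Baseline expectation is independent of group under randomisation, so its covariance with the change is unaltered. Hence r(pooled) = r(within) / 1.379, a factor of about 0.72.

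**Step 3: check by simulation** (20,000 trials, 58 per group, two-sided 0.05).

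- Within-arm r = 0.3: mean pooled r is 0.215, against 0.298 within arm. The correlation is detected in 65% of trials when pooled, against 91% within arm.
- Within-arm r = 0: mean pooled r is 0.00 and the false-positive rate is 5.1%.

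Pooling therefore dilutes a real association but does not create one.

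**Step 4: what adjustment would gain.** Take SD 1.0 as the residual SD before expectation is added. Adding expectation multiplies it by √(1 − r²).

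| Assumed r | Pooled r | Variance removed (r²) | Residual SD | Power at 58 per group |
|---|---|---|---|---|
| none | – | – | 1.000 | 0.898 |
| 0.1 | 0.07 | 1% | 0.995 | 0.901 |
| 0.2 | 0.14 | 4% | 0.980 | 0.910 |
| 0.3 | 0.22 | 9% | 0.954 | 0.923 |
| 0.4 | 0.29 | 16% | 0.917 | 0.941 |

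These powers are for the test against the 1.3-point margin used in 2.2. Against a difference of zero, power under the planning figures is already essentially 1, so adjustment would only narrow the interval.

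**The case against.** The strongest reply is that the label has no analytic consequence. The between-group tests in 11.1.5 are for VAS at 2 and 5 minutes and for ROM; expectation is handled separately and its correlation is called exploratory. Item (2) of 11.1.5 compares demographic and other baseline values, which could already cover it. Details such as time point and pooling are commonly left to a statistical analysis plan, which is not at hand. All of this stands, and it keeps the point minor. It does not make a pre-treatment score an outcome, and it does not supply adjustment for group and baseline pain.

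Three stronger readings are tempting, and the protocol does not support them.

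- *A reader might infer that the correlation mixes the treatment effect into the expectation score.* That needs the arms to be pooled, which is not stated. Even if they were, steps 2 and 3 show dilution and no spurious association.
- *A reader might infer that expectation is left wholly unused as a covariate.* Item (4) could admit it. However, it would do so only after a significant imbalance or a significant effect on efficacy has been seen, and it does not name expectation. That is selection on the data and no substitute for prespecification.
- *A reader might infer that expectation is a rival explanation for the AA versus SAA difference.* Expectation measured before allocation is balanced on average by randomisation, so omitting it cannot bias the comparison. Expectation that diverges after allocation would be a matter of unblinding. The protocol addresses that separately, through blinding (2.4) and the end-of-treatment blinding questionnaire (5.4.2, item 4), and adjusting for the baseline score would not resolve it.

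**Conclusion.** The point holds as a minor one. Item (3) of 5.4.2 is misclassified on the face of the text. The one analysis named for expectation is weaker than a model that the same section already uses for the primary outcome.

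The size is small. If the arms were pooled, a within-arm correlation would be seen at about 72% of its value. Adjustment would lift power against the margin from about 0.90 to 0.90–0.94 for r between 0.1 and 0.4. The first figure rests on pooling, on a Pearson correlation with VAS change, and on the planning values in 2.2. The second rests on an assumed correlation for which the protocol gives no value, and on SD 1.0 being the residual SD before expectation is added. If SD 1.0 describes the change before baseline pain is accounted for, the absolute powers shift but the proportional reduction in residual SD at a given r does not, provided r is read as the correlation remaining after baseline pain.

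**What to change.** 1. In 5.4.2, remove item (3) from the secondary outcomes, and list the expectation score with the baseline characteristics in 11.1.3.
2. In 11.1.5, replace the correlation with a prespecified supportive ANCOVA: VAS change from baseline to 10 minutes on group, baseline VAS and expectation score. Report the expectation slope and the adjusted group difference, each with a confidence interval. The primary ANCOVA stays as it is.
3. If effect modification is of interest, add one further model with a group × expectation term, labelled exploratory.

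The cost is a change of wording and one extra regression on data that will be collected anyway. The drawback is that the interaction estimate will be imprecise with about 58 per group, so neither a null nor a positive result for it should carry weight.
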